## Abstract

**Background:**

The incidence of hemiparetic limb dysfunction reaches 85% in stroke patients, emerging as a critical factor influencing their daily lives. However, the effectiveness of current rehabilitation treatments is considerably limited, particularly in patients with upper extremity impairment. This study aims to conduct a prospective clinical trial to validate the safety and effectiveness of gamma oscillations induced by 40-Hz visual-auditory stimulation in treating post-stroke upper limb dysfunction and to explore the relevant mechanisms.

**Methods:**

This trial is a prospective, randomized controlled, double-blind study. All enrolled patients were randomly assigned to two groups. The experimental group received intervention through 40-Hz visual-auditory stimulation, while the control group underwent intervention with randomly matched visual-auditory stimulation frequencies. The primary efficacy endpoint is the change in motor function. Secondary efficacy endpoints include motor-evoked potentials, cerebral hemodynamic changes, neural network connectivity, and alterations in synaptic-related genes. Safety evaluation included major adverse events, all-cause mortality, and photosensitive epilepsy. Assessments will be conducted at baseline, after a 14-day treatment period, and during subsequent follow-up visits (at 3 and 6 months) post-treatment. The differences between the two groups will be compared.

**Discussion:**

This study will evaluate the safety and efficacy of gamma oscillations induced by 40-Hz visual-auditory stimulation in treating patients with upper extremity dysfunction after an acute cerebral stroke. Concurrently, we will explore potential mechanisms, including changes in synaptic-related genes and neural network connectivity. This trial is expected to provide evidence for the effectiveness of this new technique in treating upper extremity dysfunction after a stroke and improving patients’ quality of life.

**Trial registration:**

The study protocol has been registered with the Chinese Clinical Trial Registry (ChiCTR) under registration number ChiCTR2300076579 on October 12, 2023.

## Administrative information

Note: the numbers in curly brackets in this protocol refer to SPIRIT checklist item numbers. The order of the items has been modified to group similar items (see http://www.equator-network.org/reporting-guidelines/spirit-2013-statement-defining-standard-protocol-items-for-clinical-trials/).

## Introduction

### Background and rationale {6a}

Stroke remains the second-leading cause of death all over the world, characterized by a high incidence, high fatality rate, significant disability rate, and a high rate of recurrence. From 1990 to 2019, the absolute number of incident strokes globally increased by 70.0%, prevalent strokes increased by 85.0%, and deaths due to stroke increased by 43.0% [1, 2]. Stroke imposes a tremendous economic burden globally. It is reported that in high-income countries, household income loss due to stroke accounts for approximately one-third, while in upper-middle-income countries, it amounts to around half. In low-income countries, income losses attributed to stroke represent about 15% of the global total (largely due to their significantly lower income levels compared to high-income countries) [3]. Acute ischemic stroke, constituting approximately 80% of all strokes, presents a therapeutic challenge with suboptimal outcomes. Despite significant breakthroughs in vascular reperfusion techniques, including thrombolysis and thrombectomy, in the treatment of ischemic stroke [4, 5], the limited treatment window (benefiting less than 3% of patients) [6] and constraints of mechanical thrombectomy technology (with a reperfusion rate of 13 to 18%) [7] result in limited benefits and poor prognosis, particularly for patients with major vessel occlusion or severe conditions. Ongoing efforts in medical practice focus on refining thrombolysis and mechanical thrombectomy techniques, aiming to enhance patient outcomes [8, 9].

Due to the suboptimal efficacy of stroke treatment, the disability rate associated with stroke is high. Approximately 50 to 70% of patients with stroke endure varying degrees of functional impairments, encompassing muscle weakness, sensory deficits, cognitive impairments, etc., profoundly impacting their quality of lives [10, 11]. Among them, the incidence of hemiparetic limb dysfunction reaches 85%, emerging as a critical factor influencing the therapeutic aspects of patients’ daily lives [12]. Therefore, post-stroke rehabilitation is of paramount importance. As early as the AHA/ASA guidelines in 2016, it emphatically underscored the necessity for training and education of caregivers in providing stroke patients with a comprehensive rehabilitative treatment plan [13]_._ Plenty of rehabilitation approaches are currently available, including conventional rehabilitation, mirror therapy, and neuroregulatory techniques. However, the treatment effect is quietly limited. Recently, neuromodulation techniques have gained increasing attention. Among them, repetitive transcranial magnetic stimulation (rTMS) has been reported to be effective in treating post-stroke limb function disability [14]. Unfortunately, the rehabilitation outcomes for upper limb dysfunction in post-stroke patients are suboptimal, constituting a focal and challenging aspect of current rehabilitation efforts. Approximately 33 to 66% of people with upper extremity (UE) impairments partially recover after treated by rTMS at 6 months, but only 5–20% fully recover [15]. Possibly, the unclear selection of target areas for rTMS and the lack of clarity in the relationship between neural circuit activation and reconstruction have limited its effectiveness in treating post-stroke upper limb dysfunction. Therefore, there is an urgent need to identify a safer, more effective, economical, and convenient method to enhance the rehabilitation outcomes for upper limb dysfunction.

In recent years, the notion of “gamma frequency stimulation inducing gamma neural oscillations to enhance brain function recovery” has evolved into a groundbreaking discovery within the field of neuroscience. In the year 2002, the reduction in synchronicity of gamma wave oscillations in the brains of Alzheimer’s disease (AD) patients was first reported [16]. Furthermore, genetic modifications [17] and optogenetics [18] have also been confirmed to establish a relationship between induced gamma oscillations and behavioral effects in AD mouse models. Balbi et al. found that 40-Hz optogenetic stimulation-induced gamma neural oscillations, thereby promoting motor function recovery in post-stroke mice [19]. The same conclusion has been reached by our team, and the underlying mechanism has been verified to involve rescuing functional synaptic plasticity [20]. Owing to its reliance on genetic manipulation techniques, optogenetics had been circumscribed in its clinical translational applications. Tsai et al. initially affirmed that non-invasive method, specifically 40-Hz visual-auditory stimulation, could induce gamma oscillations in the visual cortex of AD mouse models, thereby diminishing the burden of amyloid-like proteins in the brain [21]. Subsequently, they further validated that this light flicker stimulation effectively decelerates neuronal degeneration, preserved synaptic functionality, mitigated inflammatory responses in microglial cells, and enhanced memory functions in AD mice. Furthermore, similar effects were observed in auditory stimulation and combined visual-auditory stimulation [22]. Hou et al. found that the utilization of 40-Hz gamma frequency light stimulation effectively reinstated slow gamma neural oscillations in the hippocampal region of mice post-stroke and confirmed the causative relationship between gamma oscillations and post-stroke cognitive impairments. Furthermore, they concluded that this stimulatory regulatory approach safeguarded ischemic neurons by enhancing synaptic plasticity and associated long-term potentiation [23].

Based on previous foundational research, gamma oscillations show promising potential in promoting brain function recovery. Among them, 40-Hz visual-auditory stimulation is safe, is well-tolerated, and holds the greatest clinical translational prospects. As early as 2002, the 40-Hz auditory stimulation was applied to healthy individuals, revealing an augmentation in localized cerebral blood flow and substantiating the safety of 40-Hz stimulation [24]. In recent years, numerous clinical investigations had reported on the amelioration of brain function through sensory stimulation-induced gamma oscillations. Singer et al. found that the application of 40-Hz visual-auditory combined stimulation was not only safe and well-tolerated in AD patients, but also preliminary results from magnetic resonance imaging and cerebrospinal fluid proteomics analysis affirmed the efficacy of this sensory stimulation in enhancing neural network connectivity and downregulating neuroinflammatory response factors [25]. Hajos et al. also revealed that 40-Hz visual-auditory combined stimulation was effective in enhancing sleep quality and daily life activities in AD patients [26]. However, there was a lack of clinical studies applying this method to post-stroke populations and understanding the underlying mechanism of the technique.

### Objectives {7}

This study aims to conduct a prospective clinical trial to validate the safety and effectiveness of the gamma oscillations induced by 40-Hz visual-auditory stimulation in treating patients with post-stroke upper limb dysfunction and explore the relevant mechanisms.

### Trial design {8}

This trial is a prospective, randomized controlled, double-blind superiority study with pre-intervention (− t1), 2 weeks post-intervention retention (T2), 3 months (T3), and post-intervention follow-up (T4) tests. The overall design is demonstrated in Fig. 1. Patients were randomly assigned to two parallel groups with a 1:1 ratio, with the experimental group receiving intervention through 40-Hz visual-auditory stimulation, and the control group undergoing intervention with randomly matched visual-auditory stimulation frequencies. A trained researcher, blinded to the group allocation, will collect the data which is shown in Table 1. The design of this trial is in accordance with the Standard Protocol Items.

**Fig. 1 Fig1:**
[figure not shown]
Comprehensive study flowchart of the protocol

**Table 1 Tab1:**
[figure not shown]
Schedule of enrollment and follow-up points

*Intervention A* 40-Hz visual-auditory stimulation group, *Intervention B* Random frequency visual-auditory stimulation group, *HBP* high blood pressure, *DM* diabetic mellitus, *MEP* motor-evoked potentials, *CMCT* central motor conduction time, *EEG* electroencephalography, *T1* T1 weighted, *DWI* T1 weighted, Diffusion-weighted imaging, *DTI* diffusion-weighted imaging, *BOLD* blood oxygen level dependent, *CTP* computer tomography perfusion, *T1* pre-intervention, *T2* 2 weeks post-intervention retention, *T3* 3 months, *T4* 6 months post-intervention follow-up

## Methods: participants, interventions, and outcomes

### Study setting {9}

A prospective inclusion of 62 stroke patients will be carried out from October 2023 to December 2024 at the Department of Neurology, Seventh People’s Hospital, affiliated with the Shanghai University of Traditional Chinese Medicine. Each patient will be enrolled into the study after signing an informed consent form.

### Eligibility criteria {10}

#### Inclusion criteria

Age ≥ 40 years.Acute anterior circulation ischemic stroke patients meeting the following criteria:(2.1)Impaired contralateral limb motor function.(2.2)Paralysis of the affected limb with muscle strength rated at levels I–IV according to the Brunnstrom staging.Onset of symptoms within 1 week.Sign an informed consent form.

#### Exclusion criteria

Presence of acoustic-optical impairments that may hinder intervention and assessment.Individuals with aphasia or severe cognitive impairments, making normal communication difficult (MMSE scores: < 17 for illiterate, < 20 for primary education, < 22 for secondary education, and < 23 for university education).Inability to maintain an independent sitting position for at least 0.5 h or tolerate training and assessment for 1 h. Inability to tolerate visual-auditory stimulation.Individuals who have used medications affecting cortical excitability (e.g., antiepileptic drugs, sedatives, or hypnotics) in the past 3 months.Confirmed cases of mental illness, severe depression (with suicidal tendencies), or epilepsy, or a family history of mental illness or epilepsy.Severe heart, liver, kidney diseases, or infectious diseases, or a life expectancy of less than 90 days.Individuals with pre-existing motor impairments or abnormal muscle tone (MRS > 2 points).Individuals with a history of prior traumatic or musculoskeletal disorders affecting functionality.Individuals who have participated in or are currently involved in drug or device clinical trials within the last 30 days.Pregnancy.

### Who will take informed consent? {26a}

The informed consent will be conducted by experienced neurologists and signed by two sides (blinded physicians and stroke patients). The potential participant has sufficient time to read the full text of the informed consent form, and neurologists will introduce the details of the contents of the informed consent form to them. The informed consent will be signed by the patient personally or the patient’s legal representative before the study.

### Additional consent provisions for collection and use of participant data and biological specimens {26b}

After the patient signs informed consent, blood will be sampled by venipuncture of elbow from participants. The entire blood sampling process is operated by a professional neurology nurse who extracts about 2 ml.

## Interventions

### Explanation for the choice of comparators {6b}

Current conventional treatment modalities for post-stroke upper limb dysfunction, including medication and routine rehabilitation, yield suboptimal results. Prior research has confirmed that 40-Hz visual-auditory stimulation can induce stable gamma oscillations. This study aims to explore the therapeutic effects of gamma oscillations on post-stroke upper limb dysfunction, building upon the aforementioned treatments. Therefore, the experimental group will receive 40-Hz visual-auditory stimulation to induce gamma oscillations, while the control group will receive randomly frequency-matched visual-auditory stimulation without inducing gamma oscillations. To monitor the induction of gamma oscillations during the intervention, this study will concurrently monitor electroencephalography (EEG) and analyze it to ensure that the experimental group exhibits induced gamma oscillations while the control group does not.

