**Fig. 2 Fig2:**
[figure not shown]
Detailed intervention protocol

40-Hz stimulation group

Each stimulus light pulse generated by the LED light panel will have a duration of 5 ms and a pulse repetition frequency of 40 Hz (40 pulses emitted per second with a pulse interval of 20 ms). The headphones will play 40-Hz audio, and each stimulation session will last for a duration of 1 min. The stimulation group will receive a total of 12 cycles of stimulation.

(2)Random frequency visual-auditory stimulation group

Each stimulus light pulse generated by the LED light panel will have a duration of 10 ms, and the pulse repetition frequency will vary randomly between 1 and 100 Hz (random emission of 1–100 pulses per second with random pulse intervals ranging from 5 to 995 ms). The headphones will play audio with random frequencies, and each stimulation session will last for a duration of 1 min. The group will receive a total of 12 cycles of stimulation.

Continuous electroencephalogram (EEG) monitoring will be conducted throughout the intervention period to record brain electrical activity.

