### Gamma oscillation entrainment via electroencephalogram (EEG)

In this study, a 32-channel scalp EEG signal recording system (Brain Amp MR PLUS, Brain Products, Germany) with a sampling rate of 500 Hz will be utilized. The electrode positions will be based on the international 10/20 system, with CPz as the reference electrode and AFz as the ground electrode. Prior to the experiments, the impedance of all electrode channels will be adjusted to below 20 kΩ. Preprocessing of data from all subjects will be done using the Makoto pipeline and EEG Lab toolbox in MATLAB. We will assess gamma oscillation entrainment by calculating changes in power spectral density before, during, and after the intervention using custom MATLAB functions.

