## Assignment of interventions: blinding

### Who will be blinded {17a}

Procedures will be implemented to control for expectancy effects related to visual-auditory stimulation. Persons who will be masked to visual-auditory stimulation status (40-Hz stimulation vs. random frequency stimulation) are participants, authorized representative of the patient (if applicable), personnel involved in outcome assessments, follow-up, data collection, and analysis. Unmasked personnel will be the engineers who set up the stimulation protocol for the device and physicians who perform the intervention.

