## Oversight and monitoring

### Composition of the coordinating center and trial steering committee {5d}

The principal investigators (PIs) of this clinical trial are PI # 1, [name], at the Shanghai Seventh People’s Hospital, Shanghai University of Traditional Chinese Medicine, and PI # 2, [name], at the Shanghai Seventh People’s Hospital, Shanghai University of Traditional Chinese Medicine. PI #1 is responsible for designing the research project’s concept, including the stimulation protocol, synaptic-related genes, EEG, and all neurophysiological recording methods. PI #1 will also perform and analyze all neurophysiological recordings for all study participants of the clinical trial along with her research team. PI #2 is responsible for designing radiological and clinical assessments, leading the implementation of visual-auditory stimulation and regular rehabilitation training, as well as conducting clinical assessments for study participants at the hospital. The trial steering committee comprises the PIs and dedicated research staff.

The PIs and dedicated research staff will form the trial steering committee, which is responsible for overseeing and managing the entire project. The study governance for this single-site study is divided into several teams, including the oversight team, recruitment team, intervention deployment and assessment team, neurophysiological recording and neuroimaging team, blood sample team, and data management and analysis team. The oversight team, led by the PIs, has overall responsibility for the conduct and progress of the study. Each team is led by a dedicated research staff or clinician and works closely with the oversight team to establish and monitor standard operating procedures. Each team meets weekly with the PI to discuss decisions and progress within their specific area of responsibility. Full study meetings are held quarterly and as needed to ensure all aspects of the study are coordinated and progressing according to plan.

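### EEG recorded during stimulation is likely to reveal the arm, and the protocol does not keep it from the masked staff who record and analyse MEP/CMCT and off-stimulation EEG

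*Protocol article*

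**What the plan says.** All references are to the protocol article.

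- **Explanation for the choice of comparators {6b}:** EEG is monitored alongside the intervention, and the team will "analyze it to ensure that the experimental group exhibits induced gamma oscillations while the control group does not".
- **Intervention description {11a}, text under Fig. 2:** "Continuous electroencephalogram (EEG) monitoring will be conducted throughout the intervention period to record brain electrical activity". One arm has "a pulse repetition frequency of 40 Hz"; in the other, "the pulse repetition frequency will vary randomly between 1 and 100 Hz".
- **Secondary outcomes, Gamma oscillation entrainment via EEG:** entrainment is assessed by "calculating changes in power spectral density before, during, and after the intervention using custom MATLAB functions". The during-stimulation spectrum is therefore part of a listed secondary outcome.
- **Outcomes {12}:** MEPs and CMCT, measured with TMS, are classed as neurophysiological biomarkers.
- **Composition of the coordinating center and trial steering committee {5d}:** "PI #1 will also perform and analyze all neurophysiological recordings for all study participants of the clinical trial along with her research team". PI #1 also designs the stimulation protocol and the EEG methods.
- **Who will be blinded {17a}:** staff in outcome assessment, follow-up, data collection and analysis are masked. "Unmasked personnel will be the engineers who set up the stimulation protocol for the device and physicians who perform the intervention".
- **Plans for assessment and collection of outcomes {18a}:** two neurologists, blind to group, evaluate all outcomes.

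**The concern.** The blinding section has two groups of staff: the masked, who collect and analyse data, and the unmasked, who set up or deliver stimulation. In-session EEG cuts across them. It is a recording, so under the governance section it belongs to the neurophysiology staff, whose role is masked. It is also expected to differ by arm, so viewing it is close to viewing the allocation.

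This matters most for MEP. Under Motor-evoked potential (MEP), the operator searches for the hotspot, sets intensity relative to threshold, adjusts it to reach a target amplitude, and averages five traces. Someone who knows or strongly suspects the arm can influence each step without intending to. Preprocessing of EEG recorded before and after the intervention also leaves room for judgement. These endpoints carry much of the mechanistic objective. A between-arm difference in them would be hard to defend if the people measuring them could have seen the in-session signal.

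**Working it through.** The point rests on setting sections side by side; the plan gives no figure to reproduce.

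**Step 1. Does in-session EEG carry arm information?** The drives are a fixed 40 Hz and a random 1–100 Hz, and section {6b} expects gamma in one arm only. The amount of signal follows from the intervention and EEG sections: 12 cycles × 1 min × 14 sessions = 168 min of stimulation per patient. Sampling is at 500 Hz, so the highest resolvable frequency is 500 / 2 = 250 Hz, well above 40 Hz. A viewer is therefore likely to be able to infer the arm. How often that inference would be right for a single patient is not stated.

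**Step 2. Who handles it?** Section {5d} gives all neurophysiological recordings to PI #1 and the research team, and lists EEG beside the other neurophysiological methods. Section {12} puts MEP and CMCT in the same class. One group is thus assigned both the in-session EEG and the outcome MEP/CMCT.

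**Step 3. Is that group masked?** Section {17a} masks by role. Recording and analysing fall under data collection and analysis. The unmasked list covers only set-up engineers and the physicians who deliver the intervention.

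**Step 4. Can the statements all hold?** They can if in-session EEG is withheld from the people who record and analyse MEP/CMCT. No section says that it is withheld, or assigns the gamma check to the unmasked staff.

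**Step 5. Which endpoints are exposed?** MEP amplitude, latency, RMT, AMT and CMCT, and the EEG taken before and after the intervention. The during-stimulation EEG cannot be assessed blind under any arrangement, because its spectrum reflects the stimulus.

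**Step 6. What could a bias do? (illustration)** Assume no true effect and a spurious between-arm shift of d standard deviations in one measure. Take 28 per arm (the plan's evaluable number) and a two-sided 5% t test with 28 + 28 − 2 = 54 degrees of freedom and critical value 2.005. The noncentrality is d × √(28/2).

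| Assumed shift d | Noncentrality | Probability of p < 0.05 |
|---|---|---|
| 0 | 0 | 5.0% |
| 0.2 | 0.748 | 11.4% |
| 0.3 | 1.122 | 19.7% |
| 0.5 | 1.871 | 45.1% |

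Nothing in the document supports any particular value of d.

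**The case against.** The strongest reply is that section {18a} already has two blinded neurologists evaluate all outcomes, and that {5d} describes several teams with standard operating procedures. The individual who views in-session EEG may never touch the TMS coil. Recording is also not viewing: the contrast in {6b} is at group level, and the MATLAB processing could be run after follow-up. This stands to the extent that a reader might infer that PI #1 is certainly unmasked, or is named as masked, and the text supports neither. Masking is by role, and no section says who looks at the EEG or when. The reply does not remove the problem. Section {18a} conflicts with {5d}, which has PI #1's team perform the recordings, and bias in MEP can enter at acquisition, before anyone evaluates a trace.

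Second, a random 1–100 Hz drive overlaps the 30–100 Hz gamma band given in the Discussion, so some control patients may show gamma. That is correct, and it is why identification of the arm is called likely rather than certain. But if the arms did not separate, the rationale for the comparator would fail.

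Third, an article may leave room-level masking and file access to the full protocol. That is fair for the detail. The point here is that the article itself assigns all recordings to one team and lists who is unmasked, and the two do not fit together.

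A reader might also infer that the primary result is compromised. FMA and Brunnstrom are not neurophysiological recordings, and the documents do not support extending this route to them.

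**Conclusion.** The point holds in limited form. Sections {6b}, {11a}, {5d}, {17a} and {18a} cannot all be true unless in-session EEG is kept from those who record and analyse MEP/CMCT, and the article provides no such separation. Every patient's T2 measurements follow a treatment period with recorded stimulation, so the exposure is trial-wide, but it is confined to secondary outcomes: MEP/CMCT and off-stimulation EEG.

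The conclusion rests on two readings: that recording and analysing fall under the masked roles in {17a}, and that the EEG will usually separate the arms as the protocol intends. Whether bias would occur, and how large it would be, is unknown. The 11% to 45% range shows only what the assumed shifts would produce; it is not an estimate for this trial. The change should be made, and it is a correction to secondary-outcome blinding rather than a threat to the primary analysis.

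**What to change.** 1. Reconcile {17a}, {18a} and {5d}. List anyone who views in-session EEG as unmasked.
2. Give in-session recording and the gamma check to the engineers or treating physicians who are already unmasked, and restrict those files until database lock.
3. Have MEP/CMCT and the EEG taken before and after the intervention acquired and processed under coded IDs by existing team members without access to in-session EEG. State how this fits with the two blinded neurologists in {18a}.
4. State openly that the during-stimulation EEG outcome, now listed as secondary, cannot be assessed blind, is reported as a manipulation check, and does not decide who stays in the trial or in the analysis.

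**Cost:** a reassignment of roles and control of file access, with no added patients, visits or procedures. It is intended to work within the existing teams, although the article does not give their sizes. PI #1 could not both view in-session EEG and run or analyse the outcome TMS sessions, and the double-blind description would be qualified for the during-stimulation EEG measure. With 2 patients included at the time of the Trial status section, nearly all recruitment was still ahead at that point.
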